### Physical activity interventions

The physical activity interventions were designed based on the Social Cognitive Theory [14]. There are two components to the physical activity intervention: 1) a brief face-to-face physical activity intervention, and 2) the 3-month mobile phone and pedometer based physical activity intervention. All women randomized into the PLUS and REGULAR groups will receive the 3-month mobile phone and pedometer physical activity intervention in an identical fashion.

#### Brief face-to-face brief intervention

Upon randomization into a 3-month mobile phone and pedometer physical activity intervention group, each woman in the PLUS and REGULAR groups will be given a face-to-face interactive session by trained research staff. The face-to-face intervention is a structured interview containing seven domains: 1) overview of the physical activity program and tailored short and long-term goal setting; 2) education about duration and intensity of brisk walking and the health benefits of exercise; 3) identification of barriers to increasing physical activity and development of strategies to overcome these barriers; 4) value and identification of social support while increasing physical activity; 5) relapse prevention; 6) education about healthy diet and weight maintenance; and 7) physical activity safety. The face-to-face intervention is designed to be interactive and actively elicits the participant's participation. An individualized written physical activity plan will be developed during the face-to-face intervention. The trained research staff will revisit and revise the plan at the 1.5- and 3-month visits.

#### Three-month mobile phone and pedometer intervention

Two different mobile phone applications were created for this RCT: the trial application (the physical activity intervention) and a content neutral run-in application. The physical activity application used during the 3-month mobile phone and pedometer intervention phase will have three components 1) the daily message/video clip, 2) daily mobile phone diary, and 3) other functions ("Talk to us", "Summary", and "Help" menus). The run-in application will mimic the format of the trial application, but will not contain any content to support a physical activity program. The run-in and trial mobile phone applications were developed to run on two different mobile phone platforms: the Java 2 platform, Micro Edition (J2ME) and the iOS (iPhone) platform. If the participant has a compatible mobile phone or an iPhone, the application is installed on their personal phone. If participants do not want to install the application on their phone or do not have a compatible mobile phone, we provide a Motorola RAZR v3xx or a Pantech LASER study mobile phone, along with voice, text messaging (short message service) and data plans.

#### Daily messages/video clips

The daily messages/video clips of the trial application reinforce the seven domains addressed in the brief face-to-face intervention; the domains are divided into twelve weekly themes (see Table 1). In order to assure the comprehensibility of the daily messages, Flesch-Kincaid Reading Grade Level (RGL) was used to assess the readability of the daily messages [15]. The daily prompts had a RGL of 4.0 or a 4th grade reading level. A pre-programmed daily message or video clip will be automatically sent at a predetermined time between 11 a.m. to 3 p.m. The daily message will be accessible on the mobile phone until 7 p.m., if no reply is made by this time, the daily message will disappear from the phone. An automated text message is generated to alert participants that the daily prompt has arrived. Each daily prompt begins with a message from the research staff, followed by a question relevant to the message. For example, on Day 5 of Week 4, subjects receive the following daily message: *'Have you let everyone around you know that you are trying to become more active so they can help you meet your goal?' *"No" or "Yes" is selected by pushing the keypad. If "No" is selected, the next screen will display "*Let others know your physical activity goal*." If "Yes" is selected, the next screen will display *"Nice work!" *It takes only 1 one to two minutes to complete the daily prompt each day.

**Table 1 T1:** Weekly themes for mobile phone application

Week 1	Monitoring daily steps/physical activity goal setting
Week 2	Identifying barriers and benefits of physical activity

Week 3	Adding a 10 minute walk

Week 4	Increasing social support for physical activity

Week 5	Building physical activity into daily activities

Week 6	Identifying community resources

Week 7	Recognizing and addressing lapses in physical activity

Week 8	Healthy diet and lifestyle tips

Week 9	Managing stress

Week 10	Maintaining motivation

Week 11	Exploring and adding new physical activities

Week 12	Wrapping-up and looking forward

#### Physical Activity diary

In our three week pilot study, the average timing of mobile diary use was approximately 9:30 pm [8], but some subjects used the mobile diary even before 8 p.m.

In this RCT, the physical activity diary will be accessible after 7 p.m. If no entry is made by 8:30 p.m., an automated text message is generated as a reminder for the participant to record the total number of steps per day and the types, and duration of physical activities.

The mobile phone diary program was designed so subjects have to answer questions sequentially. For example, when "Diary" is selected, the first question is: *"Did you wear a pedometer all day today, except for showering, swimming, or sleeping?" *If the answer is "Yes," the woman will be directed to enter the number of steps taken that day. To increase accuracy of data entry, a range of steps (1000 and 35,000) was programmed in advance. The participant will immediately receive a daily step histogram showing the daily step count, enabling her to monitor/visualize her progress. If the answer is "No" (i.e. - she didn't wear the pedometer), she will be asked to select the reason why and will receive suggestions based on her answer.

The next question is, "*Did you do more than 10 min of physical activity since midnight last night?" *If "Yes", she will be prompted to select the type and to enter the total number of minutes of physical activity. This entry generates a message providing immediate feedback based on the total number of minutes entered. For example, thirty minutes of physical activity generates the response, "Excellent job!"

#### Other functions

In addition to daily message (intervention) and mobile phone diary, the trial application includes "Summary", "Help", "Talk to us", and "Weekly goals" menu options. The "Summary" menu includes the material provided in the face-to-face intervention, the "Help" tab lists the research office contact information, and the "Talk to us" function allows the subject to directly send a text message to researchers from the application.

The activity goal is automatically updated each week and displayed in the "Weekly goals" tab on the application home screen. The mobile phone trial application automatically determines weekly daily step goals (short-term goal) by calculating a 20% step increase per week from the subject's average baseline daily steps. The long-term goal for all participants is to take at least 10,000 steps per day, seven days a week and to maintain this level of physical activity for the duration of the study.

### Physical activity maintenance

There are two different 6-month maintenance interventions, REGULAR (pedometer only) and PLUS (pedometer plus mobile phone physical activity diary). A 6-month maintenance period follows the 3-month mobile phone and pedometer based physical activity intervention; participants will be randomly assigned to one of two different maintenance interventions at the randomization visit. The maintenance intervention-REGULAR group will use the pedometer daily and the maintenance intervention-PLUS will use the pedometer and physical activity mobile phone diary daily. The purpose of the two different maintenance intervention groups is to gain insight into the "dose-response" to self-monitoring and feedback. In other words, is keeping a mobile phone diary and pedometer for 6-months a better physical activity maintenance method than a pedometer alone? The subjects in the control group continue using a pedometer for these six months of the study. The subjects in all three groups will be asked to bring back the pedometer to a research office to download the pedometer data at 5, 7 and 9 months. At the 9-month visit, participants will return all pedometers and study mobile phones (if there is any) to the research office. All participants will receive a follow-up telephone call at 12 months to assess their level of physical activity using the 7-Day Physical Activity Recall Questionnaire.

### Control group (pedometer-only group)

Participants randomized to the control group will continue using the pedometer without the intervention. Following the randomization visit, the pedometer settings will be changed so that the total steps are visible. Although providing a pedometer for the control group may temporally increase physical activity from baseline, we expect physical activity will not continue to increase in this group after the first few weeks of the study.

### Study measures

The primary outcome measure is the total steps per day as measured by the Omron Active Style Pro HJA-350IT (triaxial accelerometer) pedometer. This pedometer displays daily steps, automatically resets the step count at midnight and allows participants to view the past seven days of step counts. Data from the most recent 150 days performance are automatically stored and can be directly downloaded to a computer. The criterion for acceptable pedometer data is that the downloaded data must show that the participant wore the pedometer at least eight hours per day, and at least four days per week.

Secondary outcome measures are Intensity of Physical Activity per Day, and the Seven-day Physical Activity Recall (PAR) [16]. The Omron Active Style Pro HJA-350IT can measure activity intensity over a 60 second epoch and estimate the metabolic equivalent (METs) of the task. In this study, aerobic steps are defined as ≥ 10 min of continuous steps ≤ 3 METs (approximately > 120 steps/min). Total minutes spent in moderate (3-6 METs) and vigorous activity (≥ 6 METs) during the previous week will be used as a secondary physical activity outcome measure. An interviewer-administered PAR will be used to assess physical activities performed during the week preceding the randomization, 3 and 9-month follow-up visits and 12-month follow-up phone call.

Other study measures will be the Self-Efficacy for Physical Activity Survey [17], Social Support and Exercise Survey [18], 12-Item Short-Form Health Survey (SF-12) [19], Barriers to Being Active Quiz [20], and the Center for Epidemiological Studies Depression Scale [21].

Sociodemographic characteristics (ethnicity, marital status, date of birth, education level, employment status, annual household income, marital status, number living in the home, employment status, and health insurance status), medical history (hypertension, hyperlipidemia, etc.), current smoking status, current alcohol intake, and current medications (name and dosage) will be collected at the screening/baseline visit. All subjects will undergo a physical exam consisting of the following measures: resting blood pressure, body weight in kilograms, height in centimeters, waist and hip circumference in centimeters. For the height, weight, hip and waist circumference measurements, patients will change into a hospital gown and remove their shoes. Body mass index will be determined by dividing the body weight (kg) by the square of the height (m^2^).

A fasting blood specimen collected at baseline and at seven months will include the following tests: hemoglobin A1c, blood glucose, total cholesterol, high-density lipoprotein (HDL) cholesterol, low-density lipoprotein (LDL) cholesterol, and triglycerides.

Adverse events (AEs) will be monitored and recorded throughout the study period. An adverse events checklist will be completed at the 1.5, 3, 5, 7 and 9-month visits and the 12-month follow up call. In addition, if a subject in either intervention group has not used their mobile phone for more than seven days consecutively, they will be contacted by the research staff to assess potential adverse events (AEs). All reported AEs will be evaluated by the Principle Investigator and reported to the Data and Safety Monitoring Committee and the institution's Committee on Human Research.

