## Background

Physical inactivity is associated with an increase in cardiovascular disease, Type II diabetes, hypertension, certain types of cancer, and obesity [1-3]. The National Physical Activity Guidelines recommend at least 150 minutes a week of moderate-intensity physical activity [4]. However, approximately half of American adults, particularly women and minorities, do not meet this recommended physical activity recommendation [5].

Mobile communication technologies are widely available; the majority of adults in the United States own a mobile phone [6]. Mobile phones have the advantage of being portable and easily accessible. These are qualities that make them powerful tools for delivering physical activity interventions. Despite this considerable potential, the majority of mobile phone based physical activity intervention studies have had a relatively small sample size, have evaluated only the short-term effects of the intervention, and have been conducted without a proper control group [7-9]. Thus, it is important to systematically investigate whether mobile phone interventions work effectively, and over what period of time.

In order to better understand the feasibility and acceptability of a mobile phone based physical activity intervention, we conducted a three week pilot study on physically inactive women in the San Francisco Bay Area. The results of both quantitative and qualitative analyses of this pilot study have been published elsewhere [8,10,11]. In the pilot study, sedentary women wore a pedometer and were issued a mobile phone loaded with a custom-designed physical activity mobile phone application. In summary, this pilot study had a relatively high adherence rate for use of all components of the intervention; the pedometer, physical activity diary and response to daily messages. In addition, the women in the pilot study significantly increased their objectively measured steps over the three week observation period [8].

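### The definition of aerobic steps sets a ceiling of 3 METs but equates it with a floor on cadence; the MET sign contradicts the article's own intensity bands

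*Protocol article*

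**What the plan says.** The relevant text is in the Protocol article, Study measures. The primary outcome comes first: "The primary outcome measure is the total steps per day as measured by the Omron Active Style Pro HJA-350IT". The article then names the secondary measures: "Secondary outcome measures are Intensity of Physical Activity per Day, and the Seven-day Physical Activity Recall (PAR"). In describing what the device records about intensity, it gives the operational rule that "aerobic steps are defined as ≥ 10 min of continuous steps ≤ 3 METs (approximately > 120 steps/min"). The sentence after that gives the intensity bands and makes the minutes spent in them a secondary outcome: "Total minutes spent in moderate (3-6 METs) and vigorous activity (≥ 6 METs) during the previous week".

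Two other places show which intensity the trial is interested in. The Background cites a recommendation of "at least 150 minutes a week of moderate-intensity physical activity". The section on the brief face-to-face intervention lists, among its content, "education about duration and intensity of brisk walking and the health benefits of exercise".

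The term aerobic steps appears nowhere else in the article. No other section restates the rule or corrects it.

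**The concern.** A ceiling on energy cost cannot be approximated by a floor on stepping rate: the two halves of the definition point in opposite directions. Taken literally, the MET half gives the label aerobic to activity that the article's own bands place at or below the lower edge of moderate.

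This is an outcome definition, introduced as the rule for this study, so someone processing the pedometer files could reasonably be told to apply it. Depending on which half is followed, the variable measures slow walking, fast walking or almost nothing. In the first case, a woman who does what the intervention teaches could score lower on a measure meant to reward it. The Blinding section says that participants, staff and investigators cannot be blinded, so it is better that the choice of reading is not left open until group data are in view.

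**Working it through.** There is no planned figure to reproduce, because the point involves no sample size, power or error rate. The check is one of logic, made on the article's own terms.

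**Inputs**, all from Study measures in the Protocol article:

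- Bout length: at least 10 minutes of continuous steps.
- MET clause: intensity m ≤ 3 (an upper bound).
- Cadence clause: c "approximately > 120 steps/min" (a lower bound), given as the approximate equivalent of the MET clause.
- Bands: moderate is 3 to 6 METs and vigorous is 6 METs or more, so anything below 3 METs is less than moderate.

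**Step 1: direction of the two clauses.** Faster stepping goes with higher energy cost, so a floor on c corresponds to a floor on m. The printed MET clause is a ceiling on m. The two cannot be approximations of each other.

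**Step 2: what each reading selects.** Take bouts that meet the 10-minute condition, and assume that the article's cadence figure marks roughly the 3-MET point, as its gloss implies once the sign is turned.

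| Reading | Below 3 METs | Exactly 3 METs | Above 3 METs, moderate | Vigorous |
|---|---|---|---|---|
| MET clause alone, as printed (m ≤ 3) | in | in | out | out |
| Both clauses (m ≤ 3 and c > 120) | out | borderline | out | out |
| Cadence alone (c > 120) | out | borderline | in | in |
| MET sign turned (m ≥ 3) | out | in | in | in |

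The first reading keeps only the 3.0 boundary of the moderate band and none of the vigorous band. The second leaves few or no bouts. The third and fourth agree except near the threshold.

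**Step 3: effect on one participant.** Suppose a woman replaces one 10-minute bout below 3 METs with one 10-minute bout above 3 METs and above 120 steps/min. Her count of qualifying bouts changes as follows:

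- MET clause alone, as printed: 1 to 0, a change of −1.
- Both clauses: 0 to 0, no change.
- Cadence alone: 0 to 1, a change of +1.
- MET sign turned: 0 to 1, a change of +1.

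The same change in behaviour gives a fall, no change or a rise.

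**Step 4: which half is in error.** A lower bound at 3 METs agrees with the cadence gloss, with the moderate band that begins at 3 METs, with the brisk walking that is taught, with the moderate-intensity recommendation and with the word aerobic. The printed upper bound agrees with none of them. Turning one symbol removes every conflict.

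**Step 5: is it a fault of text extraction?** Nothing suggests so. Both inequality signs appear in the same sentence, and the lower bound for vigorous activity prints correctly in the next one.

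**The case against.** The strongest objection concerns reach, and most of it stands. A reader might infer that the trial's secondary intensity endpoint as a whole is reversed. The article does not support that. The intensity variable that it expressly assigns as a secondary outcome is the weekly minutes of moderate and vigorous activity, and that variable has its own correctly oriented bounds. Aerobic steps are defined but do not appear in the aims, the analysis section or the power section, and the article does not say how they will be analysed. The primary outcome, the power calculation and the condition for testing the maintenance period do not use them.

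A reader might also infer that the intervention will look ineffective or harmful on this measure. That follows only if the MET clause is coded alone. Coding both clauses gives a nearly empty variable, and coding cadence alone gives roughly the intended one. The surrounding text makes the intended direction fairly plain, so a careful programmer may well notice. The article also gives no MET value for brisk walking: that it lies above 3 METs is an inference from the cadence gloss and the bands.

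Two further points might be added and should not be. The bands meet at 6 METs, which could suggest double counting. This is ordinary shorthand, and if the outcome is a combined total, an epoch at exactly 6 METs counts once. Nor can it be taken as given that every 60-second epoch is kept. The article says that the device can measure intensity over such epochs and stores 150 days of data, not that each epoch is retained.

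The contradiction itself survives all of this. An article may leave detail to a fuller plan, but here it states a definition and states it inconsistently.

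**Conclusion.** The definition of aerobic steps is wrong as written: its MET clause contradicts its own cadence gloss and the article's moderate band. Under the literal MET reading, nearly all moderate and all vigorous bouts drop out, and the direction of a treatment effect on this variable could turn round. With both clauses applied, little or nothing would be expected to qualify. How far a group mean would move cannot be computed, because the article gives no distribution of bouts by intensity.

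The conclusion that the MET sign is the faulty half rests on the article's bands, its cadence figure and the activity that it teaches. The possible reversal rests on two assumptions: that the MET clause is coded alone, and that brisk walking exceeds 3 METs. The effect is limited to the derived aerobic-steps variable. Total steps per day and moderate and vigorous minutes stand as they are. The weight is minor to moderate, and no main conclusion of the trial depends on it.

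**What to change.** In Study measures, change the MET clause so that aerobic steps are bouts of at least 10 minutes of continuous steps at ≥ 3 METs, with more than about 120 steps/min kept as the approximate cadence. State that the MET threshold is the operative criterion and that the cadence is only an approximation; otherwise bouts near the threshold remain open to two readings. Writing ≥ also settles that a bout at exactly 3 METs counts.

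Then check the pedometer processing code against the corrected rule before any between-group analysis.

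The cost is one symbol and one clarifying phrase in the text, plus a code check. The change alters neither the sample size nor the visit schedule, and calls for no measurement beyond those the article already describes. If the code already uses a lower bound, only the text needs correcting. If it does not, the variable would have to be derived again from whatever intensity data have been kept.

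### A secondary outcome named per day is defined as an unscaled weekly total of active minutes, while weeks with only four wear days are accepted

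*Protocol article*

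**What the plan says.** All the relevant text is in the Study measures section of the protocol article.

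- **Name.** The outcome is introduced on a daily scale: "Secondary outcome measures are Intensity of Physical Activity per Day".
- **Definition.** It is then made operational as a sum over a week: "Total minutes spent in moderate (3-6 METs) and vigorous activity", which, counted "during the previous week will be used as a secondary physical activity outcome measure", is the analysed quantity.
- **Source.** The definition follows the statement that the device "can measure activity intensity over a 60 second epoch and estimate the metabolic equivalent (METs) of the task".
- **Acceptance rule.** Pedometer data are acceptable if the participant "wore the pedometer at least eight hours per day, and at least four days per week".

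The section on statistical analysis and power specifies linear mixed models for the primary and secondary endpoints. It states no division by valid days, scaling to seven days or adjustment for wear. The primary outcome, by contrast, is expressed as steps per day.

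**The concern.** The name and the definition are on different time bases. They are interchangeable only if every accepted week has the same number of wear days. The acceptance rule allows 4, 5, 6 or 7, so two women who are equally active each day can have quite different values.

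Two consequences follow. First, even if wear is the same in all arms, variation in wear days adds noise and pulls the recorded level down. Second, if mean wear days differ between arms, the difference enters the treatment comparison as if it were activity.

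There is a plausible route to unequal wear. The section on the physical activity diary says that users are asked each evening whether they wore the pedometer, and that a negative answer is followed up with suggestions. PLUS and REGULAR have the diary to month 3, and after that only PLUS does (section on physical activity maintenance). CONTROL has the pedometer only. Prompting about wear therefore follows arm in both main comparisons.

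**Working it through.** The article gives no expected level, standard deviation or effect in minutes for this outcome, so there is no stated figure to reproduce. The check is arithmetic on the definition.

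**Inputs from the article**
- Accepted wear days per week: d = 4, 5, 6 or 7.
- Outcome: total minutes in the week.
- Guideline level cited in the Background, used only for scale: 150 min/week.

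**Assumptions, not in the article**
- The minutes are device minutes.
- Activity is spread evenly over days, at m minutes per day.
- Non-wear days contribute no minutes.

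**Step 1: one woman, constant activity.** Recorded total = m × d. Relative to a full week, the change is d/7 − 1, whatever m is.

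| Wear days | Change | Recorded total if the true level is 150 min/week |
|---|---|---|
| 4 | 4/7 − 1 = −42.9% | 150 × 4/7 = 85.7 |
| 5 | 5/7 − 1 = −28.6% | 150 × 5/7 = 107.1 |
| 6 | 6/7 − 1 = −14.3% | 150 × 6/7 = 128.6 |
| 7 | 0% | 150.0 |

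If a woman's wear fell from 7 days to 4, her daily activity would have to rise by 7/4 − 1 = 75% for her total to stay level.

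**Step 2: two arms with equal true activity.** Spurious difference = m × (difference in mean wear days). Both factors are assumed, so a range is shown.

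| Gap in mean wear days | m = 10 min/day | m = 20 min/day |
|---|---|---|
| 0 | 0 | 0 |
| 0.5 | 5 min/week | 10 min/week |
| 1.0 | 10 min/week | 20 min/week |

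Against the 150 min/week guideline, the extremes of the non-zero range are 5/150 = 3% and 20/150 = 13%.

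**Step 3: the same data as a mean per valid day.** (m × d)/d = m for any d. A woman at a true 150 min/week gives 150/7 = 21.4 min/day with 4, 5, 6 or 7 valid days. Under the even-spread assumption, the dependence on wear days disappears.

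**The case against.** The strongest reply is that this is a condensed article. The per-day name suggests that a daily rate was meant, and the handling of incomplete weeks is commonly left to the full protocol or analysis plan. A daily rate may well have been intended. But the article does not leave the scale open: it fixes a total, and that total conflicts with the outcome's own name.

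A second reply is that the harm rests on unstated premises. The defining sentence does not name the device, and the next sentence concerns the recall questionnaire. The device reading is still the natural one, because the preceding text describes the device's intensity measurement. Nor does the article say whether minutes from days with under eight hours' wear are dropped or counted. Counting them would shrink the effect but not remove it. This stands as a limit on the size.

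Third, a reader might infer that the outcome is shown to be biased in favour of the arm with the diary. The documents do not support that. They report no wear by arm, all arms have a pedometer for nine months, and REGULAR and CONTROL are also expected to keep using it. Randomisation also requires at least 80% adherence to eight-hour wear in the run-in, about 0.8 × 7 = 5.6 days a week. That does not guarantee later wear, but it makes a contrast of 7 days with 4 an extreme one. The 43% compares two individual weeks, not two arms.

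Fourth, a reader might infer that using one week per visit is itself an error, since the device stores 150 days. It is not. The pre-visit week is a legitimate choice that lines up with the recall questionnaire. Pooling all weeks between visits would change the question while step goals are rising by 20% a week.

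**Conclusion.** The point holds as a flaw in the stated definition of one secondary outcome. Its name is daily, its definition is an unscaled weekly total, and the acceptance rule lets the number of contributing days run from 4 to 7. At constant activity, the recorded value is 43%, 29% or 14% lower with 4, 5 or 6 wear days than with 7. These percentages assume device minutes, even spread over days and no minutes from non-wear days; they are smaller if short-wear days are counted.

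Added noise and a lower level follow whenever wear varies, even if it is equal across arms. Between-arm bias is conditional: it needs mean wear to differ, which is plausible from the diary prompts but not quantified. The 5 to 20 min/week range therefore illustrates assumed gaps and assumed activity levels. It is not an estimate for this trial. The primary outcome, sample size and power are not touched.

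**What to change.** Replace the defining sentence with one that sets the outcome as mean minutes of moderate plus vigorous activity per valid wear day (at least eight hours' wear) in the week before the visit, among weeks that meet the four-day minimum. Multiply by seven if a weekly figure is wanted for comparison with the guideline or the seven-day recall. State that minutes from days below the eight-hour threshold are excluded, so that numerator and denominator refer to the same days.

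This reconciles the definition with the outcome's name and puts it on the same daily scale as the primary outcome. The cost is a sentence or two of text and a small programming change on data already downloaded. One assumption remains: activity on worn days must represent activity on unworn days. Reporting the number of valid days per week by arm and visit would let readers judge that.

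### The extra adverse-event contact for phone non-use covers the intervention arms only and has no end date, so adverse-event ascertainment may be unequal by arm

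*Protocol article*

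**What the plan says.** The adverse-event paragraph under Study measures opens with a general commitment: "Adverse events (AEs) will be monitored and recorded throughout the study period". It then gives a schedule without restriction by arm: "An adverse events checklist will be completed at the 1.5, 3, 5, 7 and 9-month visits and the 12-month follow up call".

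A second route is added. Research staff contact a woman to ask about adverse events "if a subject in either intervention group has not used their mobile phone for more than seven days consecutively". The sentence names the intervention groups only and sets no end to the period in which it operates.

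Three other sections bear on how the rule works:

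- Physical activity maintenance, on months 3 to 9: "The maintenance intervention-REGULAR group will use the pedometer daily and the maintenance intervention-PLUS will use the pedometer and physical activity mobile phone diary daily".
- Control group: "Participants randomized to the control group will continue using the pedometer without the intervention".
- Three-month mobile phone and pedometer intervention: for a woman with a compatible handset, "the application is installed on their personal phone". Her phone may therefore be her own everyday phone.

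Data management and security describes a daily report, reviewed by the team, on compliance with the trial application. It describes no means of seeing other phone use. Blinding says that research staff cannot be blinded.

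**The concern.** If one arm is asked about adverse events more often than another, it can report more of them at the same true rate. Here the extra enquiry depends on allocation by a written rule, and the staff who make the contact know the allocation. An excess of minor events in the intervention arms could then reflect detection and not harm, and nobody could tell which unless the source of each event was recorded.

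The maintenance period adds a second difficulty. After month 3 a REGULAR woman who does exactly what is asked has no diary to complete. If the rule is read as application use and still runs, following her assignment is what triggers a safety call, whereas a PLUS woman who keeps her diary never triggers one. If the rule is dropped for REGULAR alone, only PLUS keeps the extra surveillance. In either case unscheduled staff contact would also fall unevenly on the two arms that the second aim compares.

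**Working it through.** The article gives no adverse-event rate, power figure or contact count on this point, so there is no stated figure to reproduce. The check sets the sections side by side and adds simple arithmetic.

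**1. Scheduled ascertainment (Study measures).** Months 1.5, 3, 5, 7, 9 and 12 make 6 occasions. Three of them (5, 7 and 9) fall in maintenance. None is limited to an arm.

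**2. Women eligible for the triggered contact (Randomization; Study measures).** 192 / 3 = 64 per arm. PLUS + REGULAR = 64 + 64 = 128 eligible; CONTROL = 0 of 64.

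**3. What the rule implies after month 3, by reading.**

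| Reading | REGULAR, adherent | PLUS, adherent | CONTROL |
|---|---|---|---|
| Application use; rule continues for both arms | meets the trigger continuously | does not meet it | not covered |
| Application use; rule kept only where a phone task is assigned | not covered | covered, does not meet it while adherent | not covered |
| Any phone use; rule continues | depends on ordinary phone use | does not meet it | not covered |
| Rule ends at month 3 | not covered | not covered | not covered |

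The first two readings give REGULAR and PLUS different surveillance, in opposite directions. The fourth gives none. The third builds in no difference in coverage, but the documents describe no way to observe it. The asymmetry against CONTROL holds in months 0 to 3 under every reading.

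**4. How often the trigger could be met under the first reading.** More than seven days means at least eight. Six months is 6 × 30.4375 ≈ 183 days, and 183 / 8 = 22.9, so at most 22 complete eight-day windows. This is a ceiling on windows and not a forecast of calls. The article does not say whether one unbroken spell of non-use leads to one contact or to repeated ones.

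**5. Possible effect on reported counts.** Let r be the share of true events caught by the common checklist, and q the share of the missed events that the extra contact recovers, averaged over all women in the arm. With equal true rates:

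ratio = (r + (1 − r)q) / r

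Example: r = 0.7, q = 0.5 gives (0.7 + 0.3 × 0.5) / 0.7 = 0.85 / 0.7 = 1.21.

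| r | q = 0 | q = 0.25 | q = 0.50 | q = 0.75 |
|---|---|---|---|---|
| 1.0 | 1.00 | 1.00 | 1.00 | 1.00 |
| 0.9 | 1.00 | 1.03 | 1.06 | 1.08 |
| 0.7 | 1.00 | 1.11 | 1.21 | 1.32 |
| 0.5 | 1.00 | 1.25 | 1.50 | 1.75 |

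Both r and q are assumptions; the documents give neither. If few women trigger the rule, q is near zero and so is the distortion.

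**The case against.** The strongest reply is that the article plans no between-arm comparison of adverse events. They are not listed among the primary, secondary or other measures. The statistical section models only the primary and secondary endpoints, and events go to the investigator, the safety committee and the ethics committee as oversight. That is correct, and no flawed test can be alleged. It does not remove the risk, because any tabulation by arm, including one read by the safety committee, carries the same unequal detection.

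Second, the common checklist is the main ascertainment and covers all arms. This stands, and it limits the possible distortion.

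Third, CONTROL has no phone intervention, and pedometer data are downloaded only at the research office, so no comparable real-time signal of silence exists there. Staff contact already differs in months 0 to 3 because the intervention arms have a face-to-face session and plan revisions. This explains the asymmetry but does not make the counts comparable.

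Some stronger readings are tempting but not supported:

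- *Counts do differ by arm.* The documents show unequal opportunity only.
- *REGULAR meets the trigger by design after month 3.* This needs use to mean application use and the rule to run into maintenance. The article states neither, and a check only on women who stop an assigned phone task is a natural alternative.
- *REGULAR would receive a call every week, about 26 in six months.* The threshold is more than seven days, which caps the windows at 22, and repeat calls are not stated.
- *The step comparison is biased.* Uneven staff contact is possible, but nothing in the article shows an effect on steps.

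**Conclusion.** The point holds in limited form. A written rule gives 128 planned intervention women a route to adverse-event detection that 64 CONTROL women lack, with no end date. Ascertainment may therefore be unequal between the intervention arms and CONTROL.

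Inequality between REGULAR and PLUS is conditional on how use is defined and on whether the rule runs past month 3. On that, Study measures and Physical activity maintenance leave an unresolved ambiguity; it is not a declared design feature.

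The size cannot be determined from the documents. The illustrative ratios run from 1.00 to 1.08 if the checklist catches at least 90% of events, and reach 1.32 at 70% and 1.75 at 50%, for q up to 0.75. The efficacy aims and the sample size are not called into question. The change is still worth making, because the source of an event is hard to reconstruct if it was not recorded at the time.

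**What to change.** 1. Reconcile Study measures with Physical activity maintenance: state what counts as using the phone, and whether and how the trigger applies to each maintenance arm after month 3. That choice belongs to the investigators. Switching the trigger off for REGULAR alone would not solve the problem, since PLUS would then be the only arm with extra surveillance.
2. Record the source of each adverse event (scheduled checklist or triggered contact) and log every triggered contact by arm.
3. At each scheduled visit or call, use the common checklist in all arms to elicit every event since the last one, including events already reported through a triggered contact. Without this step, setting triggered events aside would remove intervention-arm events that the next checklist would have caught, while the same events in CONTROL still counted. The bias would then run the other way.
4. Base any by-arm summary on checklist-elicited events, and list separately those known only from a triggered contact.
5. Continue to report all events to the safety committee, whatever their source.

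The cost is a sentence or two in the protocol, one field on the adverse-event form, a contact log, and a slightly smaller count in the comparative table. No safety information is lost.
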